**NOTE: A dose is defined as TWO separate 15mcg intramuscular (IM) vaccine injections, totaling 30mcg**

### SAMPLE SIZE:

140 children and youth to obtain at least 120 evaluable\* subjects

\*Evaluable subjects are defined as having received two doses of **Influenza A (H1N1) 2009 Monovalent Vaccine** 21-28 days apart and had all HAI samples collected up to and including Day 10 post Dose #2 within the protocol specified windows.

### POPULATION:

HIV-1 perinatally infected\*\* children and youth ( $\geq 4$  years to  $<25$  years of age). Subjects not on ARV therapy should not have received ARVs within 90 days prior to vaccination nor plan to initiate ARVs within the next 60 days. Subjects on ARVs must have been on a stable ARV regimen for at least 90 days prior to vaccination with no intention of modifying the regimen within the next 60 days.

\*\*For inclusion into the study, if perinatal acquisition of HIV infection cannot be confirmed based on the child's medical record, it is acceptable to enroll the child if the investigator's assessment is that the most likely route of infection was perinatal.

### STRATIFICATION:

Subjects will be stratified by age (at least 40 evaluable subjects per group)  
Group 1:  $\geq 4$  years to  $< 9$  years  
Group 2:  $\geq 9$  years to  $<18$  years  
Group 3:  $\geq 18$  years to  $< 25$  years

### REGIMEN:

In Step I, the initial dose of **Influenza A (H1N1) 2009 Monovalent Vaccine** will be administered to all eligible subjects during the study entry visit (Day 0) as a 30mcg dose; (given as TWO 15mcg intramuscular injections). Step II is the second dose of **Influenza A (H1N1) 2009 Monovalent Vaccine** as a 30mcg dose, administered as TWO 15mcg IM injections, 21-28 days after vaccine Dose #1. If a woman becomes

pregnant prior to Dose #2, she will not receive Dose #2 at Day 21, but will defer vaccine Dose #2 to  $\geq 14$  weeks of gestation.

Note: A second set of inclusion/exclusion criteria must be met prior to administration of Dose #2.

STUDY DURATION:

All subjects will be followed for 7 months from enrollment. Women, who become pregnant before receiving Dose #2 of study vaccine, will have study vaccine held until they are  $\geq 14$  weeks of gestation, and then they will be followed until up to 28 days after delivery. Their infant(s) will have a study visit within the first 28 days of life.

OBJECTIVES:

Primary

1. To determine the safety and immunogenicity after each of two doses of **Influenza A (H1N1) 2009 Monovalent Vaccine** in HIV-1 perinatally infected children and youth.

Secondary

1. To correlate vaccine response with baseline antibody titer.
2. To assess persistence of antibody response 6 months after Dose #2 of **Influenza A (H1N1) 2009 Monovalent Vaccine**.
3. To correlate immune responses with CD4+ cell count, CD4%, ARV use, plasma HIV-1 RNA concentration at the time of first immunization, and with timing of seasonal influenza vaccine.
4. To assess cell-mediated immune responses to **Influenza A (H1N1) 2009 Monovalent Vaccine**.
5. To describe influenza-like illness (ILI) occurring during the course of the study period, through clinic visits for all acute febrile and respiratory illnesses, including collection of respiratory specimens for determination of influenza with RT-PCR.
6. To explore factors related to HIV and its treatment that might affect the responses to H1N1 vaccinations.”

## 1.0 INTRODUCTION

### 1.1 Background

#### The Nature of Influenza Pandemics.

The dissemination of animal influenza A viruses in human populations [including subtypes A/H5N1, H7N7, H9N2 and, most recently, H1N1 swine-origin influenza virus; also designated “**2009 H1N1 Influenza A**” herein] has added urgency to ongoing efforts to develop plans for responding to potential influenza pandemics (1-4). Three pandemics have occurred during the last century. During the 1918 influenza A/H1N1 pandemic, an estimated 40 million deaths occurred worldwide (5;6). Excess mortality, high morbidity, and social disruption were all noted during the 1957 influenza A/H2N2 and the 1968 influenza A/H3N2 pandemics (7). In both of these pandemics, human populations lacked significant levels of pre-existing immunity to the pandemic virus, resulting in rapid spread of the novel influenza A virus subtypes. Thus, the emergence of a new influenza subtype in a human population has the potential to produce a public health emergency. The **2009 H1N1 Influenza A** has reached pandemic levels as defined by the World Health Organization (“an influenza virus that is causing sustained community level outbreaks in at least two countries in at least two WHO regions”) (8). Animal models indicate that **2009 H1N1 Influenza A** virus replicates better in the lung and the gastrointestinal tract compared with seasonal H1N1, suggesting that the pandemic virus may cause higher morbidity than the seasonal one. The virulence of the pandemic strain in humans is still uncertain.

The cornerstones of pandemic influenza preparedness include enhanced surveillance for the identification of emerging viruses, expanded capacity to produce and deliver relevant vaccines, availability of antiviral medications for prevention and treatment of infections caused by pandemic viruses, and improved public health infrastructure to manage and coordinate control efforts. The threat of pandemic influenza in 1976 (swine influenza) and again in 1977 (Russian influenza) resulted in an unadjuvanted inactivated influenza virus vaccine development program that provided important insights into variables influencing the immune responses to immunization (5;6). These included dosage of hemagglutinin (HA) in the vaccine, the number of doses administered to a vaccinee (1 or 2), and the type of vaccine administered (whole virus, split virus, or purified surface antigen). Host factors that influence immune responses included age, prior priming, and presence of underlying disease and immunosuppressive medications.

#### Immune Response to Influenza Vaccines.

Hemagglutinin (HA) is the viral receptor that binds to the host’s epithelial cell receptor, allowing the virus to enter the host cell. Hence, antibodies to the HA play a major role in protective immunity to influenza virus infection (9;10), and are the basis for the licensure of influenza vaccines. Resistance to infection with seasonal influenza virus strains correlates directly with both serum hemagglutination inhibition (HAI) and neutralizing

(Nt) antibody levels. Measurements of serum HAI and Nt antibodies are used to assess the immunogenicity of both seasonal and pandemic influenza vaccines (9;10).

The magnitude of the immune response to a unadjuvanted inactivated influenza vaccine is greatly affected by the dosage of antigen (usually expressed as weight of HA) contained in the vaccine. Studies evaluating the effect of HA dosage on immune responses to seasonal unadjuvanted inactivated influenza vaccines performed over the past 35 years demonstrated dose-related increases in serum and mucosal antibody responses (10-18). Higher vaccine dosages are also associated with the development of higher levels of serum antibodies that recognize antigenically distinct drift variants (18) and can overcome suboptimal responses in immunologically challenged vaccinees, such as elderly patients (17;19;20).

The effect of HA dosage on the immunogenicity of inactivated vaccines targeting some potential pandemic influenza virus strains (H9N2, H5N1) has been evaluated (21-23). Although higher doses of HA routinely induce a significantly greater response than a single dose, the response may still be poor if the antigen is not highly immunogenic. For example, H5N1 vaccines are much less immunogenic than seasonal vaccines or H9N2 vaccines, and two doses of 90mcg of either recombinant baculovirus-expressed H5N1 HA or of an inactivated subvirion antigen vaccine elicited antibody responses in only approximately 50% of young healthy adult subjects (21;22). Higher dosages of HA are also associated with more frequent adverse events.

The route of administration may affect the immune response. Intranasal administration of live attenuated or virosomal vaccines has been purported to enhance local responses including those of HIV-1 infected patients (24;25). Intradermal administration of unadjuvanted inactivated influenza vaccines generates higher antibody titers compared with intramuscular administration of the same HA-containing preparations (26-28).

The use of adjuvants is another approach to improve the immunogenicity of influenza vaccines (29;30). Adjuvants have the potential to improve serum immune responses at a given dose of antigen, to decrease the amount of antigen needed in the vaccine (dose-sparing), and to improve the immune responses by groups that generally respond poorly to inactivated antigens (e.g., immunocompromised, elderly) (31). New and more potent adjuvants have not been evaluated in HIV-infected patients.

#### Novel Pandemic Strain of Influenza.

Recently, a novel swine-origin influenza A/H1N1 virus, now designated **2009 H1N1 Influenza A**, was identified as a significant cause of febrile respiratory illnesses in Mexico and the United States (US) (3;4;6). In a recent report of severe respiratory disease concurrent with the circulation of **2009 H1N1 Influenza A** in Mexico, individuals of all ages were affected. However, compared to prior influenza seasons, the greatest increase in mortality occurred in children and young adults. It rapidly spread to many countries around the world, prompting the World Health Organization to declare a pandemic on June 11, 2009 (8). Serologic data from several cohorts in different age groups that

received the licensed seasonal trivalent influenza vaccine (TIV) suggest that these vaccines are unlikely to provide protection against the new virus (32). However, approximately 33% of adults older than 60 years of age have measurable levels of serum HAI or Nt antibody against the **2009 H1N1 Influenza A**, whereas young adults and children completely lack protective titers. These data indicate the need to develop vaccines against the new **2009 H1N1 Influenza A** strain that will be suitably protective for persons in different age groups; especially for those with one or more risk factors for severe disease.

#### Influenza in HIV-1 Infected Patients.

HIV-1 infected patients not only suffer the morbidity typical of seasonal influenza and potential interference with their HIV therapy, but there is also the potential for influenza infection that is more severe than that typical of age-matched uninfected people (33;34). Madhi et al have reported that severe lower respiratory tract infections are significantly more likely to occur in HIV-infected children than in HIV-uninfected children (RR 8.03, 95% CI: 5.05-12.76) (35). HIV-1 infected patients may also shed virus for greater periods of time and demonstrate continued infectivity and necessitate isolation in the clinic or hospital (36).

#### Response to Seasonal Influenza Vaccine in HIV-1 Infected Patients.

The antibody responses to seasonal TIV are blunted in HIV-1 infected children and adults who are not receiving antiretroviral therapy (ART) (37-39). In patients who do not have progressive HIV-1 disease and/or are receiving highly active ART (HAART), these responses are improved (40-42). Efficacy of seasonal influenza vaccine in HIV-infected patients has been established in four controlled trials (43).

#### Guillain-Barré Syndrome Associated with Influenza Vaccine.

Guillain-Barré syndrome has not typically been considered a complication of seasonal influenza vaccination. However, an excess of Guillain-Barré syndrome was reported in association with vaccine against the novel 1976 swine influenza strain that prompted mass immunization in preparation for a possible pandemic (44;45). National surveillance uncovered a total of 1098 patients with onset of Guillain-Barré syndrome from October 1, 1976, to January 31, 1977. A total of 532 patients had recently received an A/New Jersey influenza vaccination prior to their onset of Guillain-Barré syndrome. The estimated attributable risk of vaccine-related Guillain-Barré syndrome in the adult population was just under one case per 100,000 vaccinations (46). This experience will dictate certain features of the safety assessment planned for this protocol.

This protocol has been developed in collaboration with the Department of Microbiology and Infectious Diseases (DMID). DMID has sponsored a parallel study of **Influenza A (H1N1) 2009 monovalent vaccine** in healthy children in the United States. Vaccine timing, immunogenicity assays and vaccine safety measures will occur in both studies. Significant toxicity events in one study will impact all ongoing H1N1 vaccine studies.

## 1.2 Rationale

### 1.21 Overview

1. HIV infection increases the risk of complications from influenza infection, especially secondary bacterial infections.
2. Data with other vaccines such as Hepatitis B virus (HBV) vaccine have suggested that increasing antigen titer of the vaccine dose improves antibody response in HIV infected individuals. Higher doses of inactivated HBV vaccine have been shown to improve antibody response in HIV-infected youth (47).
3. Data from other populations suggests an increased antibody response to higher dosed seasonal influenza vaccine.
4. The P1088 study team believes that HIV-1 infected children and youth are at increased risk of severe illness and death from the swine-origin H1N1 influenza virus, since their HIV infection increase their risk of poor response to dosages of vaccine that are immunogenic in other populations. Use of a higher dose (30mcg) of **Influenza A (H1N1) 2009 monovalent vaccine** in this study of HIV-1 infected children and youth, will achieve scientific objectives of timely assessment of safety and immunogenicity in these high-risk populations while maximizing the potential for study participants to be protected by study vaccine from **2009 H1N1 Influenza A** virus this season.

### 1.22 Justification Discussion

It is very likely that the continuing epidemic spread of **2009 H1N1 Influenza A** infection in the US will greatly increase in the fall-winter season when social interactions and climactic conditions become even more conducive to spread of influenza viruses. While reports to date suggest that healthy individuals typically have a mild illness, underlying medical conditions including immunodeficiency appear to increase risk for severe disease and even death with pandemic H1N1 (48). Thus, knowledge of the safety and immunogenicity of the **Influenza A (H1N1) 2009 monovalent vaccine** in HIV-infected children and youth is critically important to address the health care needs of this vulnerable population.

Because seasonal influenza has been shown to cause more severe illness in HIV-infected individuals compared to that typical of age-matched uninfected people (33;34), it is likely that **2009 H1N1 Influenza A** will result in significant morbidity and possibly mortality in HIV infected individuals. Morbidity may be a direct result of the influenza virus or infection may result in secondary bacterial infections or decreased adherence to the patient's antiretroviral therapy due to the severe nausea and vomiting that may occur with pandemic H1N1 illness. Prevention of infection in this population will be critical.

It is well established that seasonal influenza infection impacts children in a community before becoming widespread in adult populations. Susceptibility to disease among young populations appears even more pronounced with **2009 H1N1 Influenza A** as one third of older adults have measurable levels of serum HAI or neutralizing antibody against the **2009 H1N1 Influenza A** while young adults and children completely lack protective titers. The serologic data is consistent with the observation that the attack rate and disease severity for the virus appears to be much higher in younger populations with relative protection of those >50 years of age.

Efforts are currently underway to evaluate **Influenza A (H1N1) 2009 monovalent vaccine** in healthy children. However, HIV-1 infected children attend schools and participate in all the activities that typically put children at such high risk for infection with influenza. Protection of HIV-1 infected children and youth from **2009 H1N1 Influenza A** will require knowledge of safety and immunogenicity of these new products in this population.

This study will assess the safety and immune response following each of the two doses of Novartis **Influenza A (H1N1) 2009 monovalent vaccine** in HIV-1 infected children and youth in the US and Puerto Rico. Two doses are thought to be required because study subjects have had no prior exposure to **2009 H1N1 Influenza A**. Because seasonal influenza vaccine often results in blunted response in HIV-1 infected persons, we have opted to investigate the higher dose of antigen, 30mcg, in comparison to the 15mcg dose that is currently being studied in ongoing trials of the **Influenza A (H1N1) 2009 monovalent vaccine** in healthy children. We have also opted to stratify our study population into 3 groups based on age. The groups were selected to provide information across all age groups and with knowledge that there would be insufficient power to compare immune response across age groups. This study is limited to HIV-1 perinatally infected children and youth.

In order to understand the mechanism of disease and protection, we will investigate the seroresponse, duration of response, and development of influenza-like illness following vaccine in this population. We also propose investigation of the cell-mediated response to vaccine. The generation of cytotoxic T lymphocyte (CTL) responses against **2009 H1N1 Influenza A** is of particular interest, because this virus replicates better in lung tissue than seasonal influenza and CTLs are the major mediator of viral clearance in the lungs. Memory B cells to **2009 H1N1 Influenza A** will ensure that the host responds adequately to exposure to the wild type virus.

In summary, **2009 H1N1 Influenza A** is likely to infect a significant proportion of HIV-1 infected children and youth if an effective vaccine is not available

before infection is widespread. Infection will likely lead to severe disease in this vulnerable population, therefore, vaccine efforts are critical. Immunogenicity of the candidate **Influenza A (H1N1) 2009 monovalent vaccine** must be established in HIV-1 infected children in order to assure that this population is protected. Lack of a protective immune response would support the need for additional measures to protect this high risk population.

### 1.3 Risks and Benefits of the Study

See section 9.3 for detailed information on risks and benefits of the vaccine.

## 2.0 STUDY OBJECTIVES

### 2.1 Primary Objectives

1. To determine the safety and immunogenicity after each of two doses of **Influenza A (H1N1) 2009 monovalent vaccine** in HIV-1 perinatally infected children and youth.

### 2.2 Secondary Objectives

1. To correlate vaccine response with baseline antibody titer.
2. To assess persistence of antibody response 6 months after Dose #2 of **Influenza A (H1N1) 2009 monovalent vaccine**.
3. To correlate immune responses with CD4+ cell count, CD4%, ARV use, plasma HIV-1 RNA concentration at the time of first immunization, and with timing of seasonal influenza vaccine.
4. To assess cell-mediated immune responses to **Influenza A (H1N1) 2009 monovalent vaccine**.
5. To describe influenza-like illness (ILI) occurring during the course of the study period, through clinic visits for all acute febrile and respiratory illnesses, including collection of respiratory specimens for determination of influenza with RT-PCR.
6. To explore factors related to HIV and its treatment that might affect the responses to H1N1 vaccinations.

### 3.0 STUDY DESIGN

This is a multi-center, open label, Phase II study in 140 children and youth, aged  $\geq 4$  years to  $<25$  years old in the US and Puerto Rico, who were infected with HIV-1 via perinatal transmission. The purpose of the study is to investigate the safety, reactogenicity, and immunogenicity of a two dose regimen of **Influenza A (H1N1) 2009 monovalent vaccine**.

Subjects do not need to be receiving ARV therapy but if they are receiving ARVs, they must have been on a stable ARV regimen for at least 90 days prior to vaccination with no intention to modify the regimen within the next 60 days. Changes in dosage due to weight changes or formulation are acceptable. The site should contact the team ([[contact]](mailto:[contact])) for other modifications. Additionally, if they are not currently receiving ARVs, the subject should not have received ARVs within 90 days prior to vaccination nor plan to initiate ARVs within the next 60 days.

STEP I: Subjects who meet the entry criteria for the study will receive **Influenza A (H1N1) 2009 monovalent vaccine**, 30 mcg, administered as TWO 15mcg IM injections, in either the deltoid muscle(s) or antero-lateral thigh muscle(s).\* Dose #1 will be administered on Day 0.

STEP II: Eligible subjects will receive a second dose of **Influenza A (H1N1) 2009 monovalent vaccine**, 30 mcg, administered as TWO 15mcg IM injections, in either the deltoid muscle(s) or antero-lateral thigh muscle(s).\* Dose #2 will be administered on Day 21 (+ 7 day window).

\*Only children and teens (4-18 years) may receive an injection in the antero-lateral thigh muscle (refer to the table in section 5.12 "Injection Site and Needle Size").

NOTE: For women who are found to be pregnant after receiving study vaccine Dose #1 but before study vaccine Dose #2, STEP II will be deferred until the woman is  $\geq 14$  weeks gestation. These women and their infant(s) will be followed as described in Appendix IB. Women who become pregnant after the second dose of vaccine will continue to be followed as outlined in Appendix IA.

Results of routine laboratory tests will be shared with the subject when they become available. The results of special laboratory tests, including HAI serology, other immunogenicity studies, and assessment of respiratory samples during influenza-like illness (ILI), will be batch tested, and not available until after the completion of the study. Any blood samples that are not used after 3 years following the end of the study analysis will be destroyed.

Immunogenicity of the vaccine will be primarily assessed by specific HAI titers in serum collected at baseline, after each of the 2 doses of the vaccines and at 7 months after enrollment. The assay was adapted from previously described assays developed and validated for the seasonal influenza viruses. B-cell and T-cell ELISPOT and CTL against **2009 H1N1 Influenza A virus** will be performed in a subgroup of subjects using peripheral blood mononuclear cells

cryo-preserved at the sites from blood collected at the same time points as the HAIs. These assays are also adapted from assays previously developed for seasonal influenza. At baseline and at 7 months, HAI titers and T-cell ELISPOT for the viruses contained in the seasonal vaccine and other antigens will also be measured.

The schedules of laboratory and clinical evaluations for this study are outlined in Appendices IA and IB, "Schedule of Evaluations".

**NOTE:** Other H1N1 influenza vaccines are currently under study in HIV-uninfected adults, children and youth. These vaccines include both 15mcg and 30mcg doses of adjuvanted and unadjuvanted, inactivated **Influenza A (H1N1) 2009 monovalent vaccines** from Novartis, as well as vaccines from other manufacturers. If one of the other ongoing NIH trials identifies a different preparation to be sufficiently safe and immunogenic, an additional cohort of 40 HIV-1 positive children and youth may be added to the P1088 study. However, this study will complete enrollment and vaccination of the subjects at the 30 mcg dose of Novartis study vaccine. If a new cohort is added, subjects will be followed as per the Schedule of Evaluations.

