### 8.4 Sample Size and Accrual

Approximately 140 children and youth, aged  $\geq 4$  years to 25 years old, who were infected with HIV-1 via perinatal transmission will be enrolled into this study. We will enroll at least 40 subjects each from three different age groups: age  $\geq 4$  years to  $< 9$  years of age,  $\geq 9$  years to  $< 18$  years of age and  $\geq 18$  to  $< 25$  years of age. This sample size is expected to yield at least 120 evaluable\* subjects, which will provide reasonably precise estimates of rates of adverse events and immunogenic response. Evaluable subjects are defined as having received two doses of Novartis **Influenza A (H1N1) 2009 monovalent vaccine** 21-28 days apart and had all HAI samples for collected up to and including Day 10 post second dose within the protocol specified windows.

Accrual is anticipated to be 4-6 weeks.

\*Evaluable subjects are defined as having received two doses of Novartis **Influenza A (H1N1) 2009 monovalent vaccine** 21-28 days apart and had all HAI samples for collected up to and including Day 10 post Dose #2 within the protocol specified windows.

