- Three or more subjects with abscesses or ulcerations, associated with study vaccine administration.
- Any subject with a vaccine-related SAE, as defined by ICH, as mentioned in section 7.0.
- Any subject with acute weakness of limbs and or cranial nerve innervated muscles (description of potential signal of Guillain-Barre Syndrome).

The study will also be halted for SMC review and recommendation if, during the 10 days after each vaccination, any of the following occurs:

- 15% or more (minimum of 2 if less than 20 subjects have been vaccinated) of the subjects enrolled in this study experience the same severe (Grade 3 or higher by

the DAIDS Toxicity Table) vaccine-related local reaction that interferes with daily activities. Dimensions of a local reaction are not included in stopping decisions.

- 15% or more (minimum of 2 if less than 20 subjects have been vaccinated) of the subjects in this study experience the same severe (Grade 3 or higher by the DAIDS Toxicity Table) vaccine-related quantitative systemic reactions.
- 15% or more (minimum of 2 if less than 20 subjects have been vaccinated) of the subjects enrolled in this study experience the same severe (Grade 3 or higher by the DAIDS Toxicity Table) vaccine-related subjective systemic reactions, the severity (grade) of which is corroborated by study personnel.

If the study is stopped for any of the above reasons, the SMC will instruct the protocol team under what conditions the study would stop again for a repeat of the same reason.

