## 8.6 Analyses

### 8.61 Primary Analyses

#### 8.611 Safety

The proportion of all subjects and of subjects within age strata experiencing grade 3 or grade 4 adverse events following the first and second doses of study vaccine will be presented. The precision with which these sample results estimate the rate of similar adverse events in the population represented by the study sample will be reported in terms of 90% confidence intervals (CI) around the sample proportions. This will provide 95% confidence that the rate of severe adverse effects is not greater than the upper limit of the CI around the proportion of subjects with grade 3+ events in the study sample.

Table 1 illustrates the confidence intervals for a range of hypothetical proportions of adverse events. This table shows (e.g.) that a sample finding of no grade 3+ adverse events in a total evaluable sample of 120 subjects would provide 95% confidence that the rate in the population from which the sample was drawn is no greater than 2%. A similar finding within a subsample of 20 subjects would provide 95% confidence that the population rate was no greater than 14%.

Table 1: Exact 90% Confidence Intervals around Potential Proportions of Subjects Exhibiting Grade 3+ Adverse Events (Total Sample and Selected Subsample Sizes)

| N   | Samples Rate | Lower Limit | Upper Limit |
|-----|--------------|-------------|-------------|
| 120 | 0%           | 0%          | 2%          |
|     | 5%           | 2%          | 10%         |
|     | 10%          | 6%          | 16%         |
|     | 25%          | 19%         | 32%         |
|     | 50%          | 42%         | 58%         |
| 40  | 0%           | 0%          | 7%          |
|     | 5%           | 1%          | 15%         |
|     | 10%          | 3%          | 21%         |
|     | 25%          | 14%         | 39%         |
|     | 50%          | 36%         | 64%         |
| 20  | 0%           | 0%          | 14%         |
|     | 5%           | 0%          | 22%         |
|     | 10%          | 2%          | 28%         |
|     | 25%          | 10%         | 46%         |
|     | 50%          | 30%         | 70%         |

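### The 15% halting criteria use a whole-study denominator, so a severe reaction specific to an optional added vaccine cohort of 40 could far exceed 15% of that cohort without triggering them

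*Combined protocol and SAP*

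**What the plan says.** The NOTE closing section 3.0 describes other H1N1 vaccines under study in HIV-uninfected people: "These vaccines include both 15mcg and 30mcg doses of adjuvanted and unadjuvanted, inactivated" products from Novartis, and products of other manufacturers. If another NIH trial finds a different preparation acceptable on safety and immunogenicity, "an additional cohort of 40 HIV-1 positive children and youth may be added to the P1088 study". The NOTE adds that "this study will complete enrollment and vaccination of the subjects at the 30 mcg dose of Novartis study vaccine". For the new cohort it specifies only that the Schedule of Evaluations applies.

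Section 8.5 halts the study for committee review when, in the 10 days after each vaccination, "15% or more (minimum of 2 if less than 20 subjects have been vaccinated) of the subjects enrolled in this study experience the same severe" vaccine-related local reaction of grade 3 or higher. Two parallel criteria cover quantitative and subjective systemic reactions. All three take their denominator from the study as a whole, and none mentions preparation or cohort.

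Section 8.611 reports "The proportion of all subjects and of subjects within age strata experiencing grade 3 or grade 4 adverse events", and 8.612 reports the proportion of subjects with an immunologic response. Neither mentions preparation. Section 8.4, however, defines evaluable subjects by receipt of two doses of the Novartis vaccine, and section 7.1 lists that vaccine as the only agent for which relationship must be assessed.

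**The concern.** A percentage rule protects the recipients of a product only if its denominator is the people who received that product. Here a second preparation could be introduced into a study whose three percentage rules count everyone. Recipients of the first vaccine, who cannot have a reaction to the second, would then raise the number of cases needed. The lower bar for the first 19 vaccinated subjects would not restart for the new product if the first cohort had already passed 20.

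This matters most for a product with little data in this population. Section 1.1 says of adjuvants: "New and more potent adjuvants have not been evaluated in HIV-infected patients". An adjuvanted product is one of the candidates named in 3.0, though not the only one.

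Two related gaps follow. The 15% criteria count only vaccine-related reactions, yet 7.1 requires relationship assessment only for the Novartis vaccine, so a reaction to another manufacturer's product has no stated route into the numerator. Section 8.6 also does not say whether the added cohort enters the primary proportions.

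**Working it through.** **Inputs.** Planned first cohort: "Approximately 140 children and youth" (8.4). Added cohort: 40 (3.0). Threshold: 15%, with a minimum of 2 while fewer than 20 are vaccinated (8.5). The documents give no reaction rate for either product and no start time for the added cohort. The rates below are therefore assumptions shown as ranges, and 140-first is the worst-case order.

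**The plan's own figures.** Section 8.611 illustrates precision with "a sample finding of no grade 3+ adverse events in a total evaluable sample of 120 subjects" and gives an upper limit of 2%. With zero events the exact one-sided 95% limit is 1 − 0.05^(1/N): 2.5% at N = 120, 7.2% at N = 40 and 13.9% at N = 20. These agree with the 2%, 7% and 14% in Table 1, allowing for rounding. The plan gives no operating figure for the halting criteria.

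**Cases needed.** Threshold = 0.15 × N, rounded up. Pooled: 0.15 × 180 = 27. Own denominator: 0.15 × 40 = 6. With k cases of the same reaction among the first 140, the new cohort must supply 27 − k:

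| k in first 140 | Needed among the 40 | Share of the 40 |
|---|---|---|
| 0 | 27 | 67.5% |
| 3 | 24 | 60% |
| 7 (5%) | 20 | 50% |
| 14 (10%) | 13 | 32.5% |

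**During accrual.** With 140 vaccinated and k = 0, n new subjects can meet the criterion only if n ≥ 0.15 × (140 + n). At n = 24 the requirement is 24.6, so it fails even if all 24 react. At n = 25 it is 24.75, so it can first be met there. On the cohort's own denominator, 2 cases suffice while fewer than 20 are vaccinated.

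**Chance of meeting the criterion** with all 40 vaccinated, after one dose. Pooled: X0 + X1 ≥ 27, where X0 is binomial (140, background rate) and X1 is binomial (40, new-product rate). Own: X1 ≥ 6.

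| True new-product rate | Pooled, background 0% | Pooled, 2% | Pooled, 5% | Own denominator |
|---|---|---|---|---|
| 20% | <0.1% | <0.1% | 0.2% | 83.9% |
| 30% | 0.0001% | 0.05% | 3.1% | 99.1% |
| 50% | 1.9% | 15.0% | 54.3% | >99.9% |

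**Primary proportions, only if someone pooled them.** Suppose 0 of 140 and 10 of 40 had a grade 3+ event. Pooled, 10/180 = 5.6% (exact 90% CI 3.0 to 9.2%). The new product alone gives 10/40 = 25% (14 to 39%, the N = 40 row of Table 1). The counts are assumed, and the plan does not state that this pooling would be done.

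**The case against.** **The statistical section is written for one product.** A reader might infer that the primary proportions are defined on all 180 subjects. The documents do not support that. Section 8.1 names the Novartis two-dose regimen as the subject of the study, 8.4 ties evaluability to that vaccine, and the tables use N = 120 on that basis. Another manufacturer's product would fail the definition; an adjuvanted Novartis product might meet it. Section 8.62 also treats differing responses across age strata as a reason not to pool. The accurate statement is that the plan is silent, so the pooled example above shows only what silence would permit. This objection stands.

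**Other safeguards do not depend on a percentage.** A reader might infer that harm in general would be diluted. That is also too strong. Section 8.5 pauses the study for one vaccine-related SAE, one anaphylaxis or bronchospasm, one injection-site necrosis or one case of acute limb weakness, and for small fixed counts of urticaria, abscess or ulceration. The team may pause at its discretion and reviews data every two weeks. A grade 3 event requires team approval before Dose #2 (4.45, 6.1). This also stands and narrows the point to the three percentage criteria. It does not remove the point, because those criteria address frequent severe reactogenicity that need not be serious in the regulatory sense. The SAE pause also relies on a judgement of relationship to the study vaccine, so the gap in 7.1 touches it too.

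**The cohort is a conditional placeholder.** It may never be added, its start is unstated, and another trial must first support the preparation. Sections 5.0 and 5.11 provide only for the Novartis vaccine, so further text would be needed before another product could be given. This is fair and makes the matter contingent. But the NOTE already states one rule for such a cohort and omits the halting denominator, and the expected 4 to 6 weeks of accrual in 8.4 makes a late start plausible.

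**Conclusion.** The concern holds for the three 15% criteria and the under-20 clause. Applied as worded to a cohort added after the 140, they require 27 of 40 recipients of the new product to have the same severe reaction when there are no background cases, or 20 of 40 when there are 7, instead of 6 of 40. At an assumed 30% rate the chance of meeting the criterion falls from 99.1% to between 0.0001% and 3.1% for backgrounds of 0 to 5%. The loss is smaller if the cohorts overlap in time, if background reactions are common, or if the new product's rate is very high (54.3% at a 50% rate with 5% background).

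The conclusion rests on the cohort being added without new halting text and, for the figures, on the 140-first order. It does not extend to the count-based and discretionary pauses. Entry of the added cohort into the 8.611 and 8.612 proportions, and relationship assessment for its product, are undefined and need to be settled. The current trial of 140 on one vaccine is unaffected.

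**What to change.** State in 3.0, 8.5 and 8.6 that, for any added cohort:

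- the existing 15% criteria and the under-20 clause are computed among subjects vaccinated with that preparation;
- relationship assessment covers that preparation, with 7.1 brought into line;
- its primary proportions and 90% confidence intervals are reported separately and not pooled with the 30 mcg Novartis cohort.

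This takes a few sentences and no new threshold. The cost is more frequent committee referrals for the added cohort: on its own denominator the criterion is met with probability 20.6% at a true rate of 10%, and 56.7% at 15%. Its estimates would have N = 40 precision, which Tables 1 and 3 already show. Splitting by age stratum or by dose number would not address the problem, because both products would remain in each denominator.
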